### Study measures

To evaluate intervention impacts, we will assess primary outcomes of child growth along with language, cognitive, motor, and social-emotional development milestones. Secondary outcomes of interest, which are also hypothesized to serve as mediating factors between the intervention and primary outcomes, include indicators for child health and nutrition (bone maturation, brain growth, respiratory or diarrheal infections, dietary intake, nutrient biomarkers), and responsive parenting based on observations of the home environment and parent-child interactions. Table 3 summarizes measures that correspond with outcomes of interest.

**Table 3 Tab3:** *Grandi Byen* study outcomes

Construct	Methods	Indicator	Timepoints

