**Secondary outcomes**			
Responsive parenting	Parenting Interactions with Children: Checklist of Observations Linked to Outcomes (PICCOLO); Home Observation Measurement of the Environment (HOME), mother-infant observation	PICCOLO: Scores in Responsiveness, Affection, and Encouragement HOME: environment subscale will be used to measure aspects of the household environment (i.e., availability of toys/items for child to play with) and responsive parenting.	Baseline, 6 mo, 12 mo
Child dietary intake	24-hour recall and food frequency questionnaire	Nutrient intakes, dietary diversity, and ASF consumption	Baseline, 6 mo, 12 mo (24-hour recall) Baseline, 3 mo, 6 mo, 9 mo, 12 mo (food frequency questionnaire)
Child nutrient biomarkers	Blood draw, mass spectrometry (LC-MS-MS, CP-OES)	Plasma concentrations of nutrient biomarkers	Baseline, 6 mo
Child bone maturation	Ultrasound imaging of hand and wrist	Bone age Z score	Baseline, 6 mo, 12 mo
Child brain growth	Ultrasound imaging of the head until anterior fontanelle closes	Dimensions of brain regions (gangliothalamic ovoid, biparietal diameter, corpus callosum, other standard measures)	Baseline, 6 mo
Child morbidities	Blood draw, immulite immunoassay methods Stool samples 2-week morbidity recall by mothers	Plasma concentrations of inflammatory biomarkers (ovomucoid and ovalbumin IgE, C-reactive Protein [CRP], and Insulin-like growth factor 1 [IGF-1]). Diarrhea, respiratory conditions, allergies	Baseline, 6 mo
Child genetics	Buccal swabs	Targeted genomic analyses	Baseline

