Stool samples and fecal swabs will also be essential for assessments on diarrheal and infectious outcomes, future assessment of microbiome changes, and relative biomarker changes. Samples collected at baseline and at 6- and 12-month follow-ups will be associated with assessments of current or recent (past 3 days) diarrheal disease. Our pilot data coupled with national data suggests a diarrheal prevalence of 30%, supporting adequate sampling at these intervals to estimate pathogen burden (unpublished observations—[name], Washington University School of Medicine). Stool samples will be collected from children using fecal swabs and fresh stool samples will be obtained, if available, from the child’s diaper. Should an unanticipated increase in diarrheal incidence be noted in the intervention arms, intensified efforts to identify pathogens associated with eggs (*Campylobacter* and *Salmonella*) will be pursued to determine if the egg preparations are increasing the risk of infectious diarrhea.

Ultrasound methods will be used to assess *bone maturation* at baseline and at 6- and 12-month follow-ups. *Brain growth* will also be assessed at baseline and 6 months post-enrollment using ultrasound*.* For bone maturation, ultrasound images of the child’s left hand and wrist will be obtained to assess maturity of the ossification centers. Following protocols used in our previous study in Ecuador [82], image findings will be adjusted for the child’s age and sex and indicated by the bone age Z-score (BAZ) using standards of Greulich and Pyle [83]. Additionally, brain ultrasound images will be obtained through the anterior fontanelle at baseline and 6 months. Images will assess the size of the gangliothalamic ovoid, corpus callosum, as well as ventricular diameter and extra axial space. Closure of the fontanelle will be noted, and in such cases, brain images will not be obtained. Our group conducted a feasibility study in Ecuador using a similar method [84], which will be implemented in the present study. Assessing intervention effects on child brain growth using these methods may support evidence related to DHA and choline’s role in brain development. All images will be obtained using the Mindray M7 Premium portable ultrasound with the 7L4s Linear Array Probe (Mindray North America, Mahwah, NJ).

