### Statistical analyses

#### Primary and secondary outcomes

Inferential tests will be applied in the analyses for this trial. To determine differences across the three study arms, all analyses will follow an intention-to-treat framework. Moreover, all hypothesis testing will be based on a one-sided superiority paradigm because the analyses will examine whether the study interventions have beneficial impacts for the children in the study. A one-sided superiority framework is therefore legitimate, because by the theory of change for the development of the treatment program, the intervention’s positive impacts are predictable, and efforts will be made to minimize any unintended and undesirable side-effects. Specifically, the hypothesized sign for outcome variables has a positive sign, except for the child morbidities and infection, which we hypothesize to be reduced, thus indicated by a negative sign for the coefficient.

Descriptive statistics will be used to detail baseline socio-economic, demographic, and household characteristics of the study sample. Additionally, baseline and endline characteristics for the outcomes of interest will be presented in a table with means and standard deviations or medians with interquartile ranges for continuous variables and as percentages for categorical variables. Several variables represented in summary statistics will also be used as covariates in adjusted outcome analyses to ensure a convincible level of internal validity for key study variables such as the treatment effects. Additionally, covariates will be included in analyses based on the hypothesized pathways in Fig. 2 and will also be derived empirically. Empirically derived covariates will be included in analyses when a p-value < .1 results from the likelihood ratio test or the Wald test.

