The primary analytic model to test primary hypotheses of the primary study aims—aims 1 and 2 (Table 1)—is the growth curve analysis using hierarchical linear modeling (HLM) or hierarchical generalized linear modeling (HGLM), depending on whether the outcome variable is a normally distributed continuous variable or a categorical variable. In the current study, the different timepoints (i.e., five waves of data collection at baseline and 3-, 6-, 9-, and 12-month follow-ups) are nested within children. These clustering effects violate the independent-observation assumption embedded in a linear model, so we will use HLM (also known as a random-effect or mixed-effect model) to control for the nesting structure of the data. In this study sample, there is only one child per parent, thus the nesting effect of children within families is absent. We therefore plan to treat mother-child pairs as one study level. However, we apply a two-level HLM model that treats time as level 1 and children as level 2.

Aim 3 examines the pathways to child growth and development by testing a series of mediational effects of secondary outcomes: responsive parenting, child dietary diversity and nutrient intakes, biomarker status, allergies, bone maturation, acute diarrhea, and respiratory morbidity. To conduct HLM or HGLM analysis for this aim, we will employ the multilevel analysis specially developed for testing mediational effects [89]. The analysis will involve three models: a full model, a reduced model, and a model using the mediator as a dependent variable. For the time-to-event outcomes (diarrhea episode, respiratory infections, and allergies in first 6 months of follow-up), we will use a proportional hazards model [90, 91].

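### Read literally, the blanket one-sided positive sign rule counts larger ventricles and extra-axial space as benefit in the brain-growth outcome

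*Protocol article*

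**What the plan says.** Three parts of the protocol article bear on this point.

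- **Status of the outcome.** Study measures places brain growth among the secondary outcomes, which are also described as possible mediators: "indicators for child health and nutrition (bone maturation, brain growth, respiratory or diarrheal infections, dietary intake, nutrient biomarkers".
- **What is measured.** The text under Secondary outcomes describes two cranial ultrasound examinations, one at enrolment and one six months later, made while the fontanelle is still open. On their content it says: "Images will assess the size of the gangliothalamic ovoid, corpus callosum, as well as ventricular diameter and extra axial space". It then gives the purpose: "Assessing intervention effects on child brain growth using these methods may support evidence related to DHA and choline’s role in brain development". Table 3 gives the indicator as "Dimensions of brain regions (gangliothalamic ovoid, biparietal diameter, corpus callosum, other standard measures".
- **How outcomes are tested.** Statistical analyses, Primary and secondary outcomes, says that "all hypothesis testing will be based on a one-sided superiority paradigm" and that "the hypothesized sign for outcome variables has a positive sign, except for the child morbidities and infection", the excepted outcomes being expected to fall.

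**The concern.** The gangliothalamic ovoid and corpus callosum are brain tissue. Ventricular diameter and extra-axial space measure fluid: the first inside the brain, the second between brain and skull. A larger tissue dimension can reasonably be read as growth. A larger fluid space cannot be read that way by itself, and it may reflect something other than growth.

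The sign rule makes no such distinction. It is universal apart from one exception, and that exception covers illness. If it is applied to each ultrasound measure, wider ventricles or a wider extra-axial space in an egg arm fall in the rejection region and could be offered as support for an effect of DHA and choline on the brain. What is at stake is a wrong directional inference on a mechanistic secondary outcome.

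**Working it through.** The document gives no sample size, power or alpha for brain growth, so there is no planned figure to reproduce. The check is mainly a comparison of texts.

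**Step 1: the measures, side by side.**

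| Measure | Table 3 | Text, Secondary outcomes | Kind |
|---|---|---|---|
| Gangliothalamic ovoid | named | named | tissue |
| Corpus callosum | named | named | tissue |
| Biparietal diameter | named | not named | head dimension |
| Ventricular diameter | not named; may fall under the table's open-ended last item | named | fluid space |
| Extra-axial space | not named; may fall under the same item | named | fluid space |

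Two measures are shared, one is named only in the table and two only in the text. Because the table's list is open, the two text-only measures do not contradict it. The firm mismatch is biparietal diameter.

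**Step 2: does the sign rule reach the fluid-space measures?** The rule covers outcome variables in general. Its only exception is child morbidities and infection. Table 3 lists child brain growth and child morbidities as separate constructs, so the exception does not cover brain measures. No other section gives ventricular diameter or extra-axial space a direction. The literal result is a positive, beneficial sign for both, that is, for 2 of the 4 measures in the text.

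**Step 3: does this depend on the list mismatch?** No. If the two lists were identical and both included the fluid-space measures, the rule would still give them a positive sign. The direction problem comes from the sign rule alone.

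**Step 4: illustration of size.** Assumptions: a simple comparison of two arm means, normal approximation, and a one-sided alpha of 0.05 (the document states no alpha). The 200 per arm and the effect size of 0.338 come from the Sample size section; the 0.2 SD shift is assumed. Images are not obtained once the fontanelle has closed and the number lost is not given, so 150 and 100 per arm are also shown as assumptions.

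For a true increase of d standard deviations in ventricular diameter:

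P(declared benefit) = Φ( d / √(2/n) − 1.645 )

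- n = 200, d = 0.2: 0.2/0.1 − 1.645 = 0.355, giving 0.64
- n = 150, d = 0.2: 1.732 − 1.645 = 0.087, giving about 0.53
- n = 100, d = 0.2: 1.414 − 1.645 = −0.231, giving 0.41
- n = 200, d = 0.338: 3.38 − 1.645 = 1.735, giving 0.96
- n = 150, d = 0.338: 2.927 − 1.645 = 1.282, giving 0.90
- n = 100, d = 0.338: 2.390 − 1.645 = 0.745, giving 0.77

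These figures show what the rule would do if a fluid-space measure were tested under it. They do not predict that such a shift will occur.

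**The case against.** The strongest reply is that the document never names ventricular diameter or extra-axial space as a separately tested endpoint. The text says only that the images will assess them. Table 1 contains no brain hypothesis, the growth-curve model is specified for aims 1 and 2, and the Aim 3 mediator list ("responsive parenting, child dietary diversity and nutrient intakes, biomarker status, allergies, bone maturation, acute diarrhea, and respiratory morbidity") leaves brain growth out. A positive sign for the construct of brain growth is sensible. How each dimension is oriented or combined may be set out in an analysis plan that is not shown. Baseline and endline values will also be tabulated, so a change in either direction would be visible.

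Much of this stands. It rules out saying that an enlarged ventricle will be tested as a benefit; the point has to be worded as what the rule gives when read literally. It does not remove the point. The article says that intervention effects on brain growth will be assessed with these methods, and it states a rule for all tests with a single exception. This is not detail left to a later document: an analysis plan could put it right only by departing from what the protocol says.

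Two stronger readings are tempting and are not supported. A reader might infer that Table 3 and the text hold rival definitions of brain growth; the table's open-ended last item can cover both added measures. A reader might also infer that a smaller fluid space is the favourable direction and that the plan cannot detect it; the document does not say which direction is favourable, and in a growing head a larger ventricle is not necessarily harmful. For that reason no benefit direction should be assigned either way.

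**Conclusion.** The point holds in a limited form. As written, the sign rule gives two fluid-space measures a beneficial direction that their meaning does not support, and nothing elsewhere in the article corrects it. It affects two of the four ultrasound measures named in the text, within one secondary outcome; the primary conclusions on growth and development do not change. The conclusion rests on the literal wording of the rule and on basic anatomy, not on any figure from a cited source. The probabilities in the illustration rest on an assumed alpha, assumed shifts and, for the smaller samples, assumed numbers imaged. The omission of biparietal diameter from the text is a separate and minor matter of wording.

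**What to change.** 1. In Statistical analyses, Primary and secondary outcomes, add an exception to the sign rule: ventricular diameter and extra-axial space are reported separately, two-sided and with no benefit direction.
2. Keep the positive direction for tissue measures such as the gangliothalamic ovoid and corpus callosum.
3. Use one list of brain measures in Table 3 and in the text: either add biparietal diameter to the imaging description or remove it from the table, and name the two fluid-space measures in the table instead of leaving them to its open-ended item.

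The cost is wording in three places. No new measurements are needed. The change should be made before outcome data are analysed.

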Disentangling which specific elements (psychosocial or hygiene and sanitation practices) of the intervention did most to enhance the nutrition intervention may be useful for future adaptations to other contexts. However, our emphasis will be on the effects of the bundled intervention, which is a common practice in medical research [58, 59]. In aim 3, we will explore hypothesized pathways from the interventions to growth and development impacts (Fig. 2). The *Grandi Byen* intervention is anticipated to influence parenting practices through improvements in caregiving and child stimulation, household environmental conditions for WASH, and child feeding for dietary diversity and ASF consumption, which may in turn reduce infectious disease incidence, improve bone maturation, and increase blood concentrations of critical nutrients. By contrast, the egg intervention alone may affect nutrition biomarkers, infection, or bone maturation to a lesser extent but is unlikely to strongly influence child development outcomes. Finally, children in the standard well-baby care group should show little or no impacts on growth and development.

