### Participant recruitment, eligibility, and screening

We will recruit eligible mother-infant dyads living in Cap-Haitien as well as the surrounding communities. To be eligible, mothers or caregivers must be individuals who are a minimum of 18 years old and are primary caregivers of an infant aged 6 to 8 months. Infants presenting evidence of a congenital health condition, severe disability, or severe malnourishment (weight-for-length Z-score < -3) will be excluded, because these factors may compromise child feeding and growth and can induce confounding in our results. Additionally, we will exclude children with allergies to ASFs (specifically eggs, milk, or fish) as well as those who are multi-birth infants (twin, triplet, etc.).

Prior to recruitment, potentially eligible mother-child dyads will be identified within Cap-Haitien and the three comparable communities of Petite Anse, Fort Saint-Michel, and Madeleine. The study team has conducted several studies in these communities and will draw on previously developed relationships and networks to recruit for this study in a timely manner. Community health agents, for example, regularly visit households throughout the communities and will assist in the identification and recruitment of eligible families. Additionally, medical records from the maternity and well-baby units at Fort Saint Michel clinic, and community rally posts will be used. The majority of mothers have access to cell phones, and numbers are contained in the medical records. Any information drawn from health records for mothers declining to be in the study will be destroyed.

Information sessions will be held in the communities to inform potential participants about the study. These strategies have previously enabled the team to canvas the entire catchment area and ensure all eligible mother-child pairs have equitable opportunity for entry into the study. Information sessions will be scheduled during off-work hours to better ensure all mothers have an opportunity to attend. If mothers express interest in participating, but are not able to attend the meeting, a separate enrollment date will be scheduled.

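### The 6-month brain-growth comparison exists only for children whose fontanelle is still open, so neither the intention-to-treat label nor multiple imputation makes it a randomised comparison

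*Protocol article*

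**What the plan says.** All places are in the protocol article.

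- **Age at entry** (Participant recruitment, eligibility, and screening): participants are "primary caregivers of an infant aged 6 to 8 months".
- **Scan dates** (Study measures, Secondary outcomes): brain growth "will also be assessed at baseline and 6 months post-enrollment using ultrasound". The route is stated as well: "brain ultrasound images will be obtained through the anterior fontanelle at baseline and 6 months".
- **Rule at closure** (same section): "Closure of the fontanelle will be noted, and in such cases, brain images will not be obtained". Table 3 agrees: "Ultrasound imaging of the head until anterior fontanelle closes".
- **Role of the outcome** (Study measures): the secondary outcomes, which are also hypothesised mediators, include "indicators for child health and nutrition (bone maturation, brain growth, respiratory or diarrheal infections, dietary intake, nutrient biomarkers". The Secondary outcomes section says that the scans are meant to assess intervention effects on brain growth and may bear on the role of DHA and choline.
- **Expected effect on maturation** (Study aims and hypothesized pathways): the multicomponent intervention is expected to act on parenting, hygiene and feeding, "which may in turn reduce infectious disease incidence, improve bone maturation, and increase blood concentrations of critical nutrients". For eggs alone, an effect on bone maturation is described as possible but smaller.
- **Analysis** (Statistical analyses, Primary and secondary outcomes): "To determine differences across the three study arms, all analyses will follow an intention-to-treat framework". Tests are one-sided for superiority. Missingness is first explored with logistic models, and then multiple imputation by chained equations is used to obtain unbiased results.

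**The concern.** An intention-to-treat comparison needs an outcome that is defined for everyone randomised, or missing values that can be recovered credibly. Here the follow-up image is withheld by design once the fontanelle has closed. That is decided after randomisation, in children who have by then had six months of intervention. If an intervention changes the timing of closure, the scanned children in the different arms are no longer alike, even though the arms were alike at baseline.

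At stake is how one secondary outcome is read. A difference, or a lack of one, among the scanned children could be reported as a randomised effect of eggs or of the multicomponent programme on brain growth when part of it reflects who could still be scanned. The primary outcomes do not depend on the scan.

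**Working it through.** The article states no closure rate and no expected number of scans, so there is no figure of its own to reproduce.

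**Step 1: age at the follow-up scan.** Entry age plus 6 months: 6 + 6 = 12 and 8 + 6 = 14 months, nominally.

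**Step 2: why imputation does not restore the randomised comparison.** Among children with a closed fontanelle, the share with an observed 6-month image is zero by rule. Any imputed value for them is extrapolated from children with an open fontanelle. It assumes that, given the variables in the imputation model, closed and open children have the same distribution of brain dimensions. No observed image can test this. Logistic models of missingness can show whether closure is related to arm or to baseline data, but not what the missing dimensions would have been.

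**Step 3: illustrative size.** The randomised number, 200 per arm, comes from the Sample size section. Everything else is assumed:

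- latent maturity M is standard normal in control, and a child is scanned if M < c;
- the share closed in control is 20%, 40% or 60%;
- the intervention shifts M by d = 0.2 or 0.3 SD;
- the correlation r between M and the brain measure is 0.3 to 0.5;
- the true effect on the brain measure is zero.

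Bias = r × [φ(c)/Φ(c) − φ(c−d)/Φ(c−d)], where φ and Φ are the standard normal density and distribution function. The number scanned is 200 × Φ(c) in control and 200 × Φ(c−d) in the intervention arm.

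*Smallest case (20% closed, d = 0.2, r = 0.3).* c = 0.842.
- Control: 0.2800/0.8000 = 0.350.
- Intervention: 0.3247/0.7394 = 0.439.
- Bias = 0.3 × (0.350 − 0.439) = −0.027 SD.
- Scanned: 160 and 148.

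*Largest case (60% closed, d = 0.3, r = 0.5).* c = −0.253.
- Control: 0.3863/0.4000 = 0.966.
- Intervention: 0.3423/0.2900 = 1.180.
- Bias = 0.5 × (0.966 − 1.180) = −0.107 SD.
- Scanned: 80 and 58.

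*Middle closure (40%).* The bias runs from −0.036 (d = 0.2, r = 0.3) to −0.092 SD (d = 0.3, r = 0.5).

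A simulation of the same model with r from 0.2 to 0.4 gave about −0.02 to −0.09 SD, and zero to within rounding when d = 0 or r = 0. The minus sign follows from taking r as positive; with r negative the same sizes appear with a plus sign.

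**Step 4: bias against sampling error.** In SD units the standard error of a difference is √(1/n₁ + 1/n₂).
- Smallest case: √(1/160 + 1/148) = 0.114, so the bias is 0.027/0.114 = 0.2 of a standard error.
- Largest case: √(1/80 + 1/58) = 0.172, so the bias is 0.107/0.172 = 0.6 of a standard error.

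**Step 5: loss of sample even if closure is equal across arms.** With 20%, 40% or 60% closed, 160, 120 or 80 children per arm remain. For a difference of 0.338 SD (the trial-level detectable effect in the Sample size section) and an assumed one-sided alpha of 0.05, power for a simple two-mean comparison falls from 0.96 with 200 per arm to 0.92, 0.84 or 0.69.

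**The case against.** Five points can fairly be made for the plan.

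1. **The link to maturation is not in the text.** A reader might infer that the scanned children are known to be selected on skeletal maturity. The article does not say so: it measures bone maturation at the hand and wrist and nowhere connects it to fontanelle closure. The connection is reasonable, since closure is ossification of the skull, but it is an inference. This stands, so the influence of arm on closure can only be called plausible. Infants already closed at baseline are also not selection caused by treatment.

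2. **The direction is not known.** A reader might infer that scanned children in the intervention arms would look smaller, so that a true benefit would be masked. That needs a positive relation between maturity and brain size, which the article does not give. With a negative relation the bias would favour the intervention and, under one-sided tests, could help produce a false positive. This stands.

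3. **The missing-data plan is not blind.** Missingness is explored before imputation, closure is recorded at the visit, and bone age is scheduled at 6 months whatever the state of the fontanelle. A ban on imputation therefore does not follow, and adjusting for baseline bone age alone would not capture a shift caused by treatment. This stands as to the remedy. It does not remove the problem in Step 2.

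4. **Intention-to-treat may mean only analysis by assigned arm, and the restriction is disclosed.** Partly right. But analysing the scanned children by assigned arm still compares groups formed after randomisation, and nothing in the article exempts this outcome from the general statement.

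5. **The outcome is peripheral and the bias small.** Brain growth has no hypothesis in Table 1 and is missing from the list of mediators to be tested under aim 3. The illustrated bias is well below one standard error. The formula also concerns size at follow-up; conditioning on the baseline scan would probably reduce the relevant correlation. These points limit the weight of the concern. Detailed imputation settings can be left to an analysis plan, but the scan rule and the general analysis claim are both stated in the article and do not fit together.

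**Conclusion.** The concern holds in a limited form. The follow-up brain scan falls at about 12-14 months and is not taken after closure, so the 6-month comparison is conditional on an event after randomisation. The general intention-to-treat statement and imputation under missing at random do not turn it into a randomised comparison.

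The size cannot be fixed from the article. Under the assumed ranges in Step 3 it is about 0.03-0.11 SD in either direction. It vanishes if closure does not depend on arm or is unrelated to brain size. The documents do not support the stronger conclusions that bias is certain, that it runs against the interventions, or that the trial's main results are affected. It is a modest but real limit on what one secondary outcome can show.

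**What to change.** - State that the 6-month brain comparison is among children with an open fontanelle, and exempt it explicitly from the intention-to-treat claim.
- Report the proportion closed at 6 months by arm beside it. Closure is already noted at the visit.
- Adjust the comparison for baseline dimension and age at scan. This improves precision and balance; it does not remove selection caused by treatment.
- If values are imputed for children with a closed fontanelle, present the result only as a sensitivity analysis. The imputation model should use the 6-month bone age already collected, and the imputed dimensions should be shifted away from missing at random over a stated range.

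The cost is a few sentences, one small table and one sensitivity analysis, with no new visit, scan or measurement. The price is a more modest claim for one secondary outcome.
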